**6.17 outcomes of interest and measurement**

**Dependent variables:** experience of intimate partner violence (IPV) in the form of physical, psychological, or sexual violence from the male partner is an independent variable of the study among couples.

**Physical intimate partner violence**: During data collection, pregnant women will be asked six physical intimate partner violence questions: (i) “Slap or throw something at her that could hurt her”, (ii) “Pushed shoved her or pulled her hair”, (iii) “Hit her with his fist or with something else that could hurt her”, and (iv) "Kicked, dragged, or beaten her up." (v) “Attempted to choke or burn her on purpose” and (vi) "threatened to use or actually use a gun, knife, or other weapon against her” (Abramsky et al., 2011) in the last 12 months and during the most recent pregnancy. If the mother responds to one or more of these, dichotomous dependent variables will be created from these questions.

If a pregnant mother answers one or more of these physical intimate partner violence questions, 1=yes (experienced physical intimate partner violence), and otherwise, 0=not experienced physical intimate partner violence.

**Sexual intimate partner violence**: A pregnant woman will be asked for three sexual intimate partner violence questions: whether her husband (i) physically forced her to have sexual intercourse with him when she did not want to”, (ii) “forced her with threats or in any other way to perform sexual acts she did not want,” and (iii) "physically forced to perform any other sexual acts she did not want to” (Abramsky et al., 2011) in the last 12 months and during the most recent pregnancy. If the pregnant mother answers one or more of these sexual intimate partner violence questions, 1=yes (experienced sexual intimate partner violence), and otherwise, 0=no (not experienced any sexual intimate partner violence since the start of this pregnancy).

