**Emotional/psychological violence: a** pregnant mother will be asked the following three psychological violence questions: (i) “say or do something to humiliate her in front of another person”, (ii) "threat to hurt or harm her or someone she cares about,” and (iii) insult or make her feel bad about herself” in the last 12 months and during the most recent pregnancy (Abramsky et al., 2011). If the mother responds to one of these emotional or psychological IPV questions, it will be recorded as 1 = yes; otherwise, 0=no (she has not experienced any emotional or psychological intimate partner violence during this pregnancy).

**Social support: The** Oslo-3 Social Support Scale (OSSS-3) will be used to measure the social support of women. The OSSS-3 consists of three items assessing the level of social support among women. Pregnant women will be asked, **Oslo 1**: How many people are so close to you that you can count on them if you have great personal problems? The responses will be: 1. 'None, 2. ‘1–2’ 3. ‘3–5’ 4, ‘5+’; **Oslo 2:** How much interest and concern do people show in what you do? The responses will be "none."2 ‘little’ 3 ‘uncertain’ 4 ‘some’ 5 ‘a lot’ and **Oslo 3**: How easy is it to get practical help from neighbors if you should need it? The response will be 'very difficult. 2 ‘difficult’ 3 ‘possible’ 4 ‘easy’ 5'very easy. The sum scores range from 3 to 14. Then the sum scores will be categorized as 3–8 (**poor social support**), 9–11 (moderate**social support),** and 12–14 (strong**social support**).

**Knowledge of IPV:** couples will be asked about nine items of knowledge questions on IPV. Couples who scored about 75% or above of the correct answer will be scored as “good knowledge,” and those who scored less than 75% will be scored as “poor knowledge (Oche et al., 2020).

**Attitude towards IPV**: To measure attitude toward intimate partner violence during pregnancy, couples will be asked, “In your opinion, is a husband justified in hitting or beating his wife in the following situations?" (a) “If she goes out without telling him?” (b) “If she neglects the children?” (c) “If she argues with him?” (d) “If she refuses to have sex with him?” (e) “If she burns the food?” Responses of “supportive attitude toward IPVp” to one or more of the scenarios were coded 1; “not supportive attitude toward IPVp" to all scenarios was coded '0'. (Trott et al., 2017).

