| 708 | When I am confronted with a problem, I can usually find several solutions. | | | | | | 1 | | | | 2 | | | | 3 | | | | 4 |  | | |
| 709 | If I am in trouble, I can usually think of a solution | | | | | | 1 | | | | 2 | | | | 3 | | | | 4 |  | | |
| 710 | I can usually handle whatever comes my way. | | | | | | 1 | | | | 2 | | | | 3 | | | | 4 |  | | |
|  | **PART SEVEN: experience of intimate partner violence in the recent pregnancy(last pregnancy)** | | | | | | | | | | | | | | | | | | | | |  |
| 801 | **Physical** | | | | | | | | | | | | | | | | | | |  | |  |
|  | During recent pregnancy, did your partner: | Slap you or throw something at you Yes No  that could hurt you? ………………………………1 2  Push you, shove you or pull your hair……………..1 2  Hit you with his fist or with something  else that could hurt you?..........................................1 2  Kick you, drag you about or beat you up?...............1 2  Attempt to choke you or burn you on purpose?.......1 2  Threaten to use or actually use a gun,  Knife or other weapon against you? …..…………1 2 | | | | | | | | | | | | | | | | | |  | |  |
| 802 | **Psychological** | Yes No  Say or do something to humiliate  you in front of another person?....................1 2  Threaten to hurt or harm you or  someone you care about? ………………...1 2  Insult you or make you feel bad about yourself?...1 2  Do things to scare or intimidate you  on purpose (e.g., by the way he looked at you,  by yelling and smashing things)?...................1 2 | | | | | | | | | | | | | | | | | |  | |  |
|  | During your most recent pregnancy, did your partner: |  |  |  |  |  |  |  |  |  |  |  |  |  |  |  |  |  |  |  |  |  |
| 803 | **Sexual** |  | | | | | | | | | | | | | | | | | |  | |  |
|  | During your recent pregnancy, did your partner | Yes No  Physically force you to have sexual  intercourse with him when you did not want to?.....1 2  Force you with threats or in any other way  to perform sexual acts you did not want?.............1 2  Physically force you to perform any  other sexual acts you did not want to? …………....1 2 | | | | | | | | | | | | | | | | | |  | |  |
| 804 | If a woman is yes for 801 or 802 or 803, what did you do? | Nothing……………………………………………………..…..1  Reported to him relations…………………………………….....2  Quit relationship……………………………………………...…3 | | | | | | | | | | | | | | | | | | If ‘nothing’ skip to  805 | |  |

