| 801 | **አካላዊ ጥቃት**  በቅርብ እርግዝና ወቅት, የትዳር ጓደኛዎ : | 1.አዎ 2. አይደለም  በጥፊ መትተዋሉ ወይም ሊጎዳህ የሚችል ነገር ወርውሮቦታል ?..1 2  ገፍትሯሉ፣አናዉጠዋሉ ወይም ፀጉሮትን ጎትተዋሉ……..1 2  በጥፊ ወይም በሌላ ሊጎዳዎት በሚችል ነገር መትተዋሉ?.,.1 2  መትተዋሉ፣ ጎትተዋሉ ወይስ ደብድበዋሉ?....................1 2  ሆን ብለዉ እርሶን ለማፈን ወይም ለማቃጠል ሞክረዋሉ?..1 2  በእርሶ ላይ ሽጉጥ፣ ቢላዋ ወይም ሌላ መሳሪያለመጠቀም ወይም በትክክል ለመጠቀም አስፈራርተዋሉ?....................1 2 | | | | | | | | | | |  |
| 802 | **ስነ-ልቦናዊ**  በቅርብ እርግዝና ወቅት, የትዳር ጓደኛዎ ፣ | 1.አዎ 2. አይደለም  እርሶን በሌላ ሰው ፊት ለማዋረድ አንድ ነገር ለመናገር  ሞክረዋሉ ወይስ ተናግረዋሉ?.................................1 2  እርስዎን ወይም እርስዎን የሚንከባከቡትን ለመጉዳት አስፈራርተዋሉ?………………………..……..1 2  ሰድቦዋሉ ወይም እርሶ መጥፎ ስሜት እንዲሰማ አድርገዋሉ?………………….…………………1 2  ሆን ብለዉ ማንቋሸሽ ወይም ማስፈራራት  አድርገዋል (ለምሳሌ፡ በአመለካከት  በመጮህ እና ነገሮችን በመሰባበር)?.........................1 2 | | | | | | | | | | |  |
| 803 | **ወሲባዊ**  በቅርብ እርግዝና ወቅት, የትዳር ጓደኛዎ | 1.አዎ 2. አይደል  እረሶ ሳይፈልጉ በጉልበት ወሲብ  ለመፈጸም አስገድደዋሉ?........................................1 2  በጉልበት በማስፈራራት ወይም በሌላ በማንኛዉም  መንገድ ሳይፈልጉ ወሲብ ፈጽመዋል?...................1 2  እርሲ ሳይፈልጉ በጉልበት ሌላ የወሲብ  ንክክዎችን እንድፈጽሙ አድርገዋሉ?……….…....1 2 | | | | | | | | | | |  |
| 804 | ከሶስቱ (801፣802እና 803) ብያንስ አንዱ አዎ ከሆነ፣ ምን አደረጉ? | ምንም…………………………………………………………..1  ለጓደኞቹ አመልክተዋሉ……………………………………..........2  ግንኙነት ማቋረጥ……………………………………………...…3 | | | | | | | | | | | ምንም ከሆነ ወደ 805 እለፊ |
| 805 | ምንም ካላደረጉ(ጥያቄ 804(1))፣ለምን | 2. አዎ 2. አይደለም  ሁኔታው አላግባብ የመሆኑ እርግጠኛ አለመሆን ……....1 2  ፍርሃት……………………………………………….1 2  ይቅርታ አልኩት……………………………………....1 2  ማፈር እና መሸማቀቅ…………………….………..,,..1 2 | | | | | | | | | | |  |

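### Four acts in the annexed Amharic violence items do not match section 6.17 or the English form; the clear loss to the primary outcome is a threat made only against someone the woman cares about

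*Protocol*

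**What the plan says.** The primary outcome (protocol, section 6.6.1) is experience of intimate partner violence, defined under Operational Definition as any physical, psychological or sexual violence by the husband during pregnancy. Section 6.17 lists six physical, three sexual and three psychological acts and codes each type 1 on any yes. Three of the acts read:

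- Physical, third: "Hit her with his fist or with something else that could hurt her".
- Physical, fourth: "Kicked, dragged, or beaten her up".
- Psychological, second: "threat to hurt or harm her or someone she cares about".

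The first psychological act covers both saying and doing something that humiliates her before others. The English women's form (Annex II, Part Seven) agrees with 6.17 on all four; its kick line, for example, is "Kick you, drag you about or beat you up".

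The Amharic women's form (Annex VI, Part Seven) has:

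- 801, first act: "በጥፊ መትተዋሉ ወይም ሊጎዳህ የሚችል ነገር ወርውሮቦታል".
- 801, third act: "በጥፊ ወይም በሌላ ሊጎዳዎት በሚችል ነገር መትተዋሉ".
- 801, fourth act: "መትተዋሉ፣ ጎትተዋሉ ወይስ ደብድበዋሉ".
- 802, second act: "እርስዎን ወይም እርስዎን የሚንከባከቡትን ለመጉዳት አስፈራርተዋሉ".

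On the language of the field instrument, 6.16 and 6.21 name Hadiyisa and 6.22 names Amharic. No Hadiyisa form is annexed.

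**The concern.** With an any-yes rule, the wording of each act is part of the endpoint definition. If the form put to the woman names a different act, a woman who is positive by the protocol's definition may be recorded as negative, and tabulations of single acts describe something other than what 6.17 lists. Annex VI is the only translation of the women's form in the protocol, so it is the only evidence of how these items would be put to respondents.

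**Working it through.** The check compares wording. The English readings of the Amharic below are literal glosses, which a bilingual reader should confirm.

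**Step 1: the four acts side by side**

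| Act | 6.17 and English form | Amharic form, literally | What remains covered |
|---|---|---|---|
| Physical, third | Hit with fist or a harmful object | Hit with a slap or a harmful object | Object kept; no word for fist |
| Physical, fourth | Kicked, dragged or beaten | Hit, dragged or beat | Drag and beat kept; no word for kick |
| Psychological, first | Say or do something humiliating | Tried to say, or said, something humiliating | Speech kept; no verb of doing |
| Psychological, second | Threat to her or someone she cares about | Threat to her or those who take care of her | Threat to her kept; direction of care reversed |

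The fist line uses በጥፊ, the word that the same form uses for slap two lines earlier.

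**Step 2: how many acts**

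6.17 lists 6 + 3 + 3 = 12 acts. Four are altered (4/12, one third); the other eight keep their substance.

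**Step 3: the Amharic handout (Annex IX)**

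The handout renders three of the four differently from the questionnaire. Its humiliation line has both saying and doing. Its threat line refers to a person she worries about. Its fist line speaks of his hand and is separate from the slap line. So the questionnaire wording is not simply the usual Amharic equivalent. The handout does not help on kick, which it also renders with a general verb.

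**Step 4: what each change does to the any-yes score**

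- *Threat made only against her child.* Under 6.17 she scores 1. On the Amharic form the act is not asked, so she scores 0 unless she says yes to a line describing something else. Both forms carry a fourth psychological line (scaring or intimidating), but 6.17 does not list it, so under the written rule it does not count.
- *Humiliated only by a deed.* Under 6.17 she scores 1. On the Amharic form she may still score 1 through the third psychological act (insulted, or made to feel bad). A loss is possible but not certain.
- *Punched or kicked.* The general verb in the fourth physical act covers both, so she still scores 1. What changes is the line on which she is counted.

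**Step 5: size**

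The documents do not give the share of positive women who are positive only through a lost act. First, the plan's own figure: reading the 20% decline in section 6.8 as 20 points, 37.5% against 17.5% (two-sided 5%, 80% power, no continuity correction) needs 78 per arm, and 78 × 2.3 × 1.2 = 215.3, which rounds up to the stated 216. The effective number per arm after 20% loss is 216 × 0.8 / 2.3 = 75.1.

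Now assume, without support in the documents, that a fraction f of positives is missed equally in both arms and nothing is gained:

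| f (assumed) | Control: 37.5% × (1 − f) | Intervention: 17.5% × (1 − f) | Difference: 20 × (1 − f) points | Power |
|---|---|---|---|---|
| 0 | 37.5% | 17.5% | 20.0 | 0.79 |
| 0.02 | 36.8% | 17.2% | 19.6 | 0.78 |
| 0.05 | 35.6% | 16.6% | 19.0 | 0.76 |
| 0.10 | 33.8% | 15.8% | 18.0 | 0.73 |

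This shows scale only; it does not estimate the loss.

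**The case against.** The strongest reply is that the protocol already plans the step that should catch such slips. Section 6.16 provides translators blind to the English original, an expert committee, an item-by-item rating with formal evaluation of any mean score above 3, and a pilot in 27 couples; 6.22 adds blinded back-translation of an Amharic version. Sections 6.16 and 6.21 also name Hadiyisa, so Annex VI may never reach the field. Both points stand and lower the weight of the finding. They do not make the annexed wording right, and 6.22 still points to Amharic.

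A second reply is that the any-yes rule absorbs most of the change. That holds for fist and kick, and partly for humiliation. It does not hold for the threat act.

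A third reply is that some changes widen the items: general hitting is broader than kicking, attempted speech is added to humiliation, and threats to her carers are added. This stands too. A reader might infer that prevalence is understated, but the net direction cannot be established.

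**Conclusion.** The mismatch is real and minor. Four of 12 acts in the annexed Amharic form depart from 6.17 and from the English form. One departure clearly removes cases from the primary outcome as defined: the woman whose only exposure is a threat against someone she cares about. One may remove a few more (humiliation by deed), and two mainly affect act-level results.

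Three stronger readings are tempting and not supported:

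- *The primary outcome as a whole is scored on different acts.* Eight acts are intact, and punches and kicks still score.
- *The comparison of arms is biased.* Both arms receive the same form, and nothing in the protocol suggests that the loss would differ between them.
- *Results cease to be comparable with the 37.5% used for the sample size.* That depends on how the cited Tigray study worded its items, which the protocol does not show.

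The conclusion rests on the literal reading of the Amharic and, for practical effect, on Annex VI or a form derived from it being used in the field.

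**What to change.** Before baseline:

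1. Reword the four acts in Annex VI, items 801 and 802, to match 6.17: fist in the third physical act, kick in the fourth, someone the woman cares about as the object of the threat, and both saying and doing in the humiliation act.
2. Reconcile 6.16 and 6.21 with 6.22 on whether the field form is Hadiyisa or Amharic, and carry the corrected wording into whichever is used.
3. Confirm these four items by name in the back-translation comparison already planned in 6.16.

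The cost is the rewording of four lines in a form still due for translation review and pre-test; no extra data are needed. Timing matters because 6.24 compares outcomes before and after the intervention, and a change of wording after baseline would disturb that comparison.

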**Annex vii: የባሎች መጠይቅ -አማርኛ ትርጉም**

መጠይቁ የተሞላበት ቀን (በኢት. አቆጣጠር)------------

የመጠይቅ ቁጥር--------------------

የጠያቂ መለያ ቁጥር-----------------

መጠይቁ የተጠየቀበት ቀበል-----------

መጠይቅ የተጀመረበት ሰዓት-----------

መጠይቅ ያለቀበት ሰዓት---------------

|  | | | | **ክፍል አንድ፡ ስነ ማሀበራዊ መጠጥቅ** | | | | | | | | |  |  |
| --- | --- | --- | --- | --- | --- | --- | --- | --- | --- | --- | --- | --- | --- | --- |
| መለያ  ቁጥር | | | | ጥያቄዎች | | አማራጭ መልስ | | | | | | | እለፍ |  |
| 101 | | | | አሁን ዕድሜዎት ስንት ነዉ ? | | ሙሉ ቁጥር ዕድሜ…………………………….. | | | | | | |  |  |
| 102 | | | | የት ነዉ የሚኖሩት ? | | ገጠር ………………………………………….…1  ከተማ ……………………………………………2 | | | | | | |  |  |
| 103 | | | | በትዳር ዉስጥ ምን ያክል ጊዜ ቆይተዋሉ? | | ሙሉ ዓመት/ወር…………………………… | | | | | | |  |  |
| 104 | | | | የባለቤቶት ዕድሜ ስንት ነዉ? | | ዕድሜን በሙሉ ቁጥር…………………………… | | | | | | |  |  |
| 105 | | | | ሀይማኖቶት ስንት ነዉ? | | ፕሮቴስታንት .........................................................1  ኦርቶዶክስ.............................................................2  ሙስሊም ..............................................................3  ካጦሊክ ..............................................................4  ሌላ , ይገለጽ.........................................................5 | | | | | | |  |  |
| 106 | | | | የባላቤቶት ሐይማኖት ነዉ? | | ፕሮቴስታንት .........................................................1  ኦርቶዶክስ.............................................................2  ሙስሊም ..............................................................3  ካጦሊክ ..............................................................4  ሌላ , ይገለጽ.........................................................5 | | | | | | |  |  |
| 107 | | | | ብሄሮት ምንድነዉ? | | ሀዲያ.................................................................1 ክምባታ.............................................................2  ስልጤ................................................................3  ጉራጌ.................................................................4  ሌላ, ይገለጽ......................................................5 | | | | | | |  |  |
| 108 | | | | የባለቤቶት ብሔር ምንድነዉ? | | ሀዲያ.................................................................1 ክምባታ..............................................................2  ስልጤ................................................................3  ጉራጌ.................................................................4  ሌላ, ይገለጽ......................................................5 | | | | | | |  |  |
| 109 | | | | የትምህርት ደረጃዎት ስንት ነዉ? | | ትምህርት የለም.................................................1  አንደኛ ደረጃ ትምህርት ቤት (1-8)......................2  ሁለተኛ ደረጃ ት/ቤት (9-12)………………..….3  ኮሌጅ ወይም ከፍተኛ ትምህርት ተከታትሏል …...4 | | | | | | |  |  |
| 110 | | | | የባለቤቶት ትምህርት ደረጃ ምነድነዉ? | | ትምህርት የለም...................................................1  አንደኛ ደረጃ ትምህርት ቤት (1-8)..........................2  ሁለተኛ ደረጃ ት/ቤት (9-12)………………..…….3  ኮሌጅ ወይም ከፍተኛ ትምህርት ተከታትሏል ……...4 | | | | | | |  |  |
| 111 | | | | ሥራዎት ምንድነዉ? | | ገበሬ....................................................................1  የመንግስት ተቀጣሪ..............................................2  የግል ስራ………………….…………….…….......3  ሌላ, ይገለጽ.........................................................5 | | | | | | |  |  |
| 112 | | | | የባለቤቶት ስራ ምንድነዉ? | | የቤት እመቤት ...................................................1  የመንግስት ተቀጣሪ...........................................2  የግል ስራ………………….…………………......3  ሌላ, ይገለጽ......................................................5 | | | | | | |  |  |
| 113 | | | | አማካይ የቤተሰብዎ ወርሃዊ ገቢ በብር ስንት ነው?? | | ብር በወር (የመላሽ ግምት)……………………………… | | | | | | |  |  |
| 114 | | | | ስንት ምስት አሎት? | | አንድ…………...……..………………...….......1  ሁለትና ከዚያ በላይ ……………...……….........2 | | | | | | |  |  |
|  | | | | **ክፍል አራት : የእውቀት፣የአመለካከትና ባህሪ መቖጣተር ጥያቄዎች** | | | | | | | |  | | |
| 401 | | | ስለ የቅርብ አጋር ጥቃት ሰምተዉ ያዉቃሉ? | | | | | 1.አዎ  2.አላዊቅም | | | |  | | |
| 402 | | የቅርብ አጋር ጥቃት ላይ የመረጃ ምንጮች ምንድናቸው? | | | | | | **1.አዎ 2. አይደለም**  ሚዲያ …………………….…1 2  የግል ልምድ…………......……1 2  ሆስፕታል/ጤና ጣቢያ/ጤና ኬላ..1 2  ከጤና ኤክስቴንሽ ባለሙያዎች…..1 2  ከሌክተር…………………....1 2 | | | |  | | |
| 403 | | የቅርብ አጋር( ጥቃት የህዝብ ጤና ጉዳይ ነው። | | | | | | አዎ ………………………………….1  አይደለም……………..……………..2 | | | |  | | |
| 404 | | በጥፊ መምታት፣ መምታት፣ መጎተት፣ መደብደብ፣ ማነቆ፣ መግፋት፣ ወዘተ.የፍቅር አጋር ጥቃት ምሳሌዎች ናቸው። | | | | | | አዎ ………………………………….1  አይደለም……………..……………..2 | | | |  | | |
| 405 | | የትዳር አጋሮ ባልፈለገች ጊዜ ወሲብ እንዲፈጽም ማስገደድ ወሲባዊ ጥቃት ነው። | | | | | | አዎ ………………………………….1  አይደለም……………..……………..2 | | | |  | | |
| 406 | | እሱ/እሷ የሚያዋርድ ወይም የሚያዋርድ ነገር እንዲፈጽም ማስገደድ ወሲባዊ ጥቃት ነው። | | | | | | አዎ ………………………………….1  አይደለም……………..……………..2 | | | |  | | |
| 407 | | አጋርን በሌሎች ሰዎች ፊት ማዋረድ ወይም ማዋረድ የስነ ልቦና ጥቃት ነው። | | | | | | አዎ ………………………………….1  አይደለም……………..……………..2 | | | |  | | |
| 408 | | በእርግዝና ወቅት የቅርብ ወዳጃዊ ጥቃት የእናቶች እና አዲስ የሚወለዱ ሕፃናት ላይ አሉታዊ ውጤቶች አሉት፡፡ | | | | | | አዎ ………………………………….1  አይደለም……………..……………..2 | | | |  | | |
| 409 | | የቅርብ አጋር ጥቃት የሰብአዊ መብት ጥሰት ነው። | | | | | | አዎ…………………………..………….….1  አይደለም…………………………………...2 | | | |  | | |
| **የአመለካከት ጥያቄዎች** | | | | | | | | | | | |  | | |
|  | በእርስዎ አስተያየት ባል በሚከተለው ሁኔታ ሚስቱን ለመምታት ይጸድቃል  1.አዎ  2. አይደለም | | | | | | | | | | |  | | |
| 410 | ሳትነግረው ከወጣች? | | | | | | 1 | | 2 | | |  | | |
| 411 | ልጆቹን ችላ ካላት? | | | | | | 1 | | 2 | | |  | | |
| 412 | ከሱ ጋር ብትጨቃጨቅ? | | | | | | 1 | | 2 | | |  | | |
| 413 | ከእሷ ጋር የግብረ ሥጋ ግንኙነት ለመፈጸም ፈቃደኛ ካልሆነ? | | | | | | 1 | | 2 | | |  | | |
| 414 | ምግቡን ካቃጠለች? | | | | | | 1 | | 2 | | |  | | |
| **የባህሪ መቆጣተር ጥያቄዎች** | | | | | | | | | | | |  | | |
|  | | | | |  | | | |  | | |  | | |
|  | | | | በእርስዎ አስተያየት ባል በሚከተለው ሁኔታ ምስትን በመቆጣጠር ረገድ ትክክል ነው?   1. አዎ 2. አይደለም | | | | | | | |  | | |
| 415 | | | | ከሌሎች ወንዶች ጋር ብታወራ ቅናት | | | | | | 1 | 2 |  | | |
| 416 | | | | ታማኝነት በማጣት ብከሳት | | | | | | 1 | 2 |  |  |  |
| 417 | | | | ከጓደኞቿ ጋር እንድትገናኝ አለመፍቀድ | | | | | | 1 | 2 |  |  |  |
| 418 | | | | ከቤተሰብ ጋር ያላትን ግንኙነት ለመገደብ መምከር | | | | | | 1 | 2 |  |  |  |
| 419 | | | | የት እንዳለች ለማወቅ ማጥበቅ | | | | | | 1 | 2 |  |  |  |
| 420 | | | | በገንዘብ ባያምናት | | | | | | 1 | 2 |  |  |  |
|  | | | | **ክፍል አምስት : የባሎች ተሳትፎ በቅርብ ጊዜ እርግዝና** | | | | | | | |  | | |
| 501 | | | | ከዚህ በፊት ለነበረዉ የቅርብ ጊዜ እርግዝና ባለቤቶት የቅድመ ወሊድ ክትትል አድርገዉ ነበር? | | | አዎ…………………………………….….…...1  አይደለም…………….……………….…….…2 | | | | |  | | |
| 502 | | | | አዎ ከሆነ፣ ከባለቤቶት ጋር ቢያንስ አንድ ጊዜ ቅድመ ወሊድ ክትትል አድርገዋሉ? | | | አዎ………………………………….………....1  አይደለም……………………………….….…2 | | | | |  | | |
| 503 | | | | አይደለም ከሆነ፣ ለምንድነዉ ቅድመ ወሊድ ክትትል ያላደረጉት ? (**ምርጫዎችን አይነበቡ).**  **ከአንድ መልስ በላይ ማክበብ ይቻላል**) | | | ክትትል የሴቶች ጉዳይ ስለሆነ…………………...1  ለመሄድ ጊዜ ስለለሌኝ…………………….….…2  እዉቀት ስለለለኝ…………………………..3  ማህበራዊ መገለል ስለሚደርስብኝ …………4  ስለሚፈራ/ስለምሳቀቅ……………………….....5  የኤች.አይ.ቪ ምርመራ ስለሚፈራ………….…....6  ስለማልጋበዝ……………….…………….……..7  ሌላ፣ ይገለጽ……………………………….……8 | | | | |  | | |
| 504 | | | | ባለቤትዎ የቅርብ ጊዜ እርግዝናን የት ነበር የወለዱት ? | | | ሆስፕታል--------------------------------------1  ጤና ጣቢያ------------------------------------2  ክሊኒክ----------------------------------------3  ቤት-------------------------------------------4 | | | | |  | | |
| 505 | | | | ጤና ተቋም(ሆስፕታል፣ጤና ጣቢያ ዎይም ክሊኒክ) ከሆነ፣ ባለቤቶት ስወልዱ እርሶ አብሮ ነበሩ ? | | | አዎ-------------------------------------------1  አይደለም-------------------------------------2 | | | | |  | | |
| 506 | | | | በላቤቶት ከወለዱ በሓላ ለድክረ ወሊድ እንክብካቤ አብረዉ ጤና ተቋም(ሆስፕታል፣ጤና ጣቢያ ወይም ክሊኒክ ) ሄደዉ ያዉቃሉ ? | | | አዎ-------------------------------------------1  አይደለም-------------------------------------2 | | | | |  | | |

**Annex viii: ጥንዶች ላይ የተመሰረተ ጥቃትን መከላከል ጥቅል መመሪያ-የትምህርት ጥቅል ለጥንዶች**

**መግቢያ**

የባለትዳሮች ትምህርት ፓኬጅ በሀዲያ ዞን፣ ደቡብ ምዕራብ እና ኢትዮጵያ ውስጥ ባሉ ጥንዶች በእርግዝና ወቅት የሚደርስ የቅርብ ወዳጃዊ ጥቃትን ለመቀነስ የለውጥ ሂደትን ለማገዝ የተነደፈ የመከላከያ መልእክቶች ስብስብ ነው። በእርግዝና ወቅት የቅርብ አጋሮች ጥቃትን ለመከላከል በትምህርት ሞጁል ውስጥ የተካተቱት ይዘቶች የሚከተሉትን ያጠቃልላል፡፡

- ሥርዓተ ጾታን መሠረት ያደረጉ ጥቃቶች፣
- በሴቶች ላይ የሚደርሱ ጥቃቶች እና የቅርብ አጋር ጥቃቶች።
- የጥቃት ዓይነቶች (አካላዊ፣ ጾታዊ እና ስነ ልቦናዊ ወይም ስሜታዊ ጥቃት
- በሴቶች ላይ የሚደርሱ ጥቃቶች መጠን፣ ተፈጥሮ እና በእርግዝና ወቅት የቅርብ ጓደኛሞች ጥቃትን ጨምሮ።
- ቅርብ አጋር ጥቃት እና የስልጣን እና ቁጥጥር ግንኙነት
- ሴቶች ማብቃት የሚያስከትላቸው ውጤቶች
- ሥርዓተ ጾታ፣ኃይል እና ጾታዊነት
- በእርግዝና ወቅት የአይፒቪ የተለመዱ ቀስቅሴዎችጤናማ ግንኙነትን የሚያመጣው ምንድን ነው?

